### Statistical analysis plan

Plausibility checks will be carried out prior to any data analyses.

Descriptive analyses of all included patients will be carried out after baseline visits have been completed. Analyses will be carried out for the total sample and stratified by age, gender, group allocation, and frailty status. This is intended to provide a first impression of the data distribution within the strata regarding relevant outcomes. The mean and standard deviation are shown for continuous variables, as well as relative and absolute frequencies for categorical variables.

The primary efficacy endpoint is the change in the level of care dependency—defined as the difference between the care level at baseline and 12 months post-surgery (ΔNBA Score = NBA Score (V18) – NBA Score (V2)).

The prehabilitation effect is defined and tested by a non-parametric approach using the Mann-Whitney-Wilcoxon rank sum test with ties. Moreover, sensitivity analyses will be performed using multivariable logistic regression analysis to adjust for relevant confounders at baseline (e.g., age or gender), as well as to consider longitudinal data and its correlation structure [75].

The secondary will be assessed at different time points (see Table 3, visits 1 to 18) and compared between the intervention and control groups. Moreover, generalized linear mixed-effect regression models will be used, with changes over 1 year as the dependent variable and relevant confounding variables included in the model.

Moreover, sensitivity analyses will be conducted to address the impact of the missingness mechanism, e.g., missing at random or not at random. Complete case analyses will be compared with multiple imputation analyses. Missing data prior to the follow-up measurements might occur (e.g., death, morbidity, loss to follow-up, or withdrawn consent). Death is expected to be a significant source of missing data, and it will be classified as the worst possible endpoint in terms of the level of care dependency.

The principal analyses will be performed according to the intention-to-treat principle and will not be adjusted for screening or baseline covariates or center. The significance level is set to alpha = 5% (two-side). The *p*-value, as a measure of the strength, indicates the association between the dependent and the independent variables. The null hypothesis will be rejected if the *p*-value related to the test statistic for the treatment effect is equal to or smaller than the significance level alpha = 0.05.

The full statistical analysis plan will be finalized and published on the project website after completion of the follow-up assessments, but prior to the commencement of analyses and closing of the database.

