## Methods

### Study design

This study is an assessor-blinded, two-arm parallel-group, randomized, controlled, multicenter superiority trial (RCT) in frail or pre-frail patients undergoing elective surgery in Germany with an allocation ratio of 1:1 per hospital and a follow-up period of 12 months. Currently, 19 study centers participate in the recruitment of participants. Updates will be posted on ClinicalTrials.gov and on the project homepage [28, 29].

The intervention group will receive prehabilitation in one of four different settings: (1) inpatient facilities, such as geriatric wards; (2) day clinics; (3) outpatient rehabilitation centers; or (4) home-based via a mobile rehabilitation team. A current list of participating centers and prehabilitation partners, as well as the current version of the study protocol in German and English languages (V1.1; Date: 6/13/2020), can be found online at the project homepage [28]. The flow diagram of the study is presented in Fig. 1, and the SPIRIT Checklist is provided in Additional file 2.

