### Outcome measures

The primary outcome is the level of care dependency 12 months after surgery. Care dependency is measured using the German structured assessment “Neues Begutachtungsinstrument” (NBA) [43]. The NBA is a standardized tool used by the medical service of the statutory health insurance companies in Germany to assess the need for professional help in the care of older people or people with disabilities, as well as the amount and type of care assistance required. NBA results are a prerequisite for obtaining financial assistance from the insurance for professional care assistance. The NBA consists of six domains: (1) mobility, (2) cognitive and communication ability, (3) behavior and psychological problems, (4) self-dependence, (5) disease-specific demands and burdens, and (6) daily routine scheduling and social contacts. Based on the NBA, six grades of care dependency are defined from zero (no dependency) to five (highest level of dependency) [44].

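### The primary rank test leaves out hospital and baseline care grade, giving up some precision although it remains valid and keeps its planned power

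*Protocol article*

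**What the plan says.** In the protocol article, the section *Statistical analysis plan* takes as primary endpoint the change in care level, "defined as the difference between the care level at baseline and 12 months post-surgery", and tests it with a Mann-Whitney-Wilcoxon rank sum test with ties. The same section states that the principal analyses "will not be adjusted for screening or baseline covariates or center". No reason is given. Adjusted models appear only as sensitivity analyses, with age and gender as the example covariates.

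*Study design* describes allocation "with an allocation ratio of 1:1 per hospital and a follow-up period of 12 months" and adds: "Currently, 19 study centers participate in the recruitment of participants". *Randomization* describes a web-based procedure but names neither strata nor blocks. *Outcome measures* gives care dependency six grades, 0 to 5. *Sample size and power considerations* computes 470 per group for the unadjusted rank test.

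**The concern.** Two pieces of information that the trial holds anyway are left out of the primary test.

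- **Hospital.** If allocation is balanced within hospital and outcomes differ between hospitals, the treatment comparison is free of most between-hospital variation, but the unstratified test still counts that variation in its null variance. The test then rejects a true null hypothesis less often than 5% of the time, and some power is lost.
- **Baseline grade.** Subtracting baseline is not the same as conditioning on it. On a scale bounded at 0 and 5, a patient who starts at grade 0 cannot improve and one at grade 5 cannot worsen, so the distribution of change still depends on the starting grade. A test that ignores this carries avoidable noise.

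The planned effect is small (probabilistic index 0.547), so a few points of power are worth having if they cost nothing.

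**Working it through.** **1. The plan's own figure.** Inputs are from Table 4: intervention 5 / 47.5 / 45 / 2.5%, control 2.5 / 42.5 / 50 / 5% (improved, unchanged, one level worse, two or more worse).

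- P(intervention better) = 0.05×0.975 + 0.475×0.55 + 0.45×0.05 = 0.3325.
- P(tie) = 0.00125 + 0.201875 + 0.225 + 0.00125 = 0.4294; half of it is 0.2147.
- Probabilistic index θ = 0.3325 + 0.2147 = 0.5472.
- Pooled proportions are 0.0375, 0.45, 0.475, 0.0375; the sum of their cubes is 0.1984.
- n per arm = (1.960 + 0.842)² × (1 − 0.1984) / [6 × (0.0472)²] = 470.9 with unrounded inputs. Power at 470 is 79.9% to 80.1%, depending on the variance used.
- Total = 940 / 0.70 / 0.975 = 1377.3, rounded up to 1378.

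Both stated figures reproduce.

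**2. Leaving out hospital.** Let r be the share of rank variance explained by hospital, with arms balanced within hospital. The documents give no r, so a range is assumed. The unadjusted z then has null standard deviation √(1 − r), so:

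- true alpha = 2 × [1 − Φ(1.960/√(1 − r))]
- power, unadjusted = Φ(0.842/√(1 − r))
- power, adjusted = Φ(2.802/√(1 − r) − 1.960)

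| Assumed r | True alpha, unadjusted | Power, unadjusted | Power, adjusted | Gain (points) |
|---|---|---|---|---|
| 0.01 | 0.049 | 80.1% | 80.4% | 0.3 |
| 0.02 | 0.048 | 80.2% | 80.8% | 0.6 |
| 0.05 | 0.044 | 80.6% | 82.0% | 1.4 |
| 0.10 | 0.039 | 81.3% | 84.0% | 2.7 |

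The unadjusted test never falls below its planned 80%.

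**3. Leaving out baseline grade.** This was simulated: 470 per arm, 19 hospitals of unequal size, permuted blocks of 4 within hospital, and Table 4 margins kept by a latent normal model. Baseline was a five-level ordinal variable with an assumed split of 50/15/20/10/5%. Shares refer to the latent variable behind the change categories and are assumptions.

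| Latent share: hospital, baseline | Unadjusted Wilcoxon | Rank ANCOVA, hospital | Rank ANCOVA, hospital + baseline |
|---|---|---|---|
| 0, 0 | 80.0% | 79.8% | 80.0% |
| 0, 0.10 | 80.0% | 79.8% | 81.6% |
| 0, 0.30 | 80.8% | 81.0% | 88.0% |
| 0.05, 0.30 | 80.4% | 81.1% | 88.4% |

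Conditioning on baseline gains about 2 points at a latent share of 0.10 and about 7 at 0.30. With no hospital or baseline effect, adjustment costs nothing measurable.

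**4. Alpha when only baseline is left out.** The simulated alpha of the unadjusted test was 0.045 and 0.044 at baseline shares of 0.10 and 0.30. With 3000 runs the Monte Carlo standard error is √(0.05×0.95/3000) = 0.004, so both lie within 1.5 standard errors of 0.05. That agrees with theory: a covariate not balanced by design costs power and leaves alpha alone.

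The simulation is too coarse to confirm the small alpha shifts in step 2: with hospital as the only effect, simulated alpha was 0.052 at a latent share of 0.05 and 0.038 at 0.10. The alpha figures for hospital therefore rest on the closed form.

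**The case against.** The strongest reply is that nothing is broken. The unadjusted rank test is valid, the sample size was computed for exactly this test, and adjusted analyses are planned as sensitivity analyses. All of that stands, and it limits the point to efficiency.

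The balance premise is also inferred. *Study design* states a ratio per hospital, and *Randomization* names no strata or blocks. Simple 1:1 randomisation would give the same ratio on average at each hospital, and the test would then not be conservative. This stands too, so the conservatism is conditional.

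Floor and ceiling restrict both arms alike under randomisation. They cost precision and do not bias the test.

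Stronger readings are tempting, but the documents do not support them:

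- A reader might infer that leaving out baseline also makes the test conservative. Only a factor balanced by design does that.
- A reader might infer a saving of about 100 patients per arm. For hospital that needs a share of about 100/471 = 21% of rank variance, more than twice the largest share considered here, and nothing in the documents suggests it.
- A reader might fault the wording that "sensitivity analyses will be performed using multivariable logistic regression analysis", the description of the p-value, or the absence of an effect estimate. The outcome is called ordered categorical in the sample size section. Link function and effect measure can be left to the full statistical analysis plan, and the p-value sentence is a matter of wording.

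What the reply does not supply is a reason for excluding hospital and baseline grade, which the article does as a stated decision and not by silence.

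**Conclusion.** The point holds as a modest loss of efficiency. The analysis is not invalid, and the sample size is not wrong. Hospital accounts for the smaller part: a gain of 0.3 to 2.7 power points and a true alpha of 0.049 to 0.039 for assumed shares of 1% to 10%, provided that allocation is balanced within hospital. Baseline grade probably accounts for the larger part: about 2 to 7 points for assumed latent shares of 10% to 30%, with alpha unchanged. If hospital explains 2% or less and baseline grade little, the gain is negligible. Because adjustment had no measurable cost even with no effect of either factor, the change is still worth making.

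**What to change.** Before the statistical analysis plan is finalised, and without sight of outcomes by arm, make the primary analysis one of the following and keep the unadjusted Wilcoxon test as a sensitivity analysis:

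- a van Elteren test stratified by hospital, which stays closest to the planned test but recovers only the hospital part; or
- a rank ANCOVA with hospital and baseline care grade, which recovers both parts.

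State in the plan whether randomisation was stratified or blocked by hospital, and how hospitals with very few patients are pooled.

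A proportional-odds model of the 12-month grade, with death as the worst category and baseline grade and hospital as covariates, can serve as a supporting analysis. It is less suitable as the lead. On the change scale, Table 4 implies cumulative odds ratios of (0.05/0.95)/(0.025/0.975) = 2.05, (0.525/0.475)/(0.45/0.55) = 1.35 and (0.975/0.025)/(0.95/0.05) = 2.05, so one common odds ratio would summarise the planned effect imperfectly.

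The cost is a wording change, declared as a departure from the published article, and slight extra analysis work. Hospital and baseline grade are already collected, and the sample size need not change.

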#### Interim analyses

There will be no interim analyses.

#### Health economics evaluation

A protocol detailing the methods of the health economics evaluation will be published separately. In brief, the intervention’s cost-effectiveness will be evaluated from the perspective of the statutory health insurance (payer perspective), as well as its cost utility from a societal perspective. Data on resource utilization will be collected using both a bottom-up approach (e.g., patient questionnaires, therapists’ documentation) and a top-down approach (administrative data). The prehabilitation costs (intervention group only) will be calculated using a micro-costing approach, and the costs of healthcare resource use within 12 months after surgery (both groups) will be determined using standard unit costs for the FIMA Questionnaire [76]. Costs will be expressed in euros. Different measures of effectiveness will be considered, including the quality-adjusted life years (QALYs), based on survival data and the patients’ QoL (EQ-5D-5L) scores, as well as appropriate utility weights. Probabilistic and deterministic sensitivity analyses will be performed to explore any uncertainty in the results. A cost-effectiveness acceptability curve will be drawn to determine if prehabilitation is cost-effective under different willingness to pay assumptions.

### Management committee and data safety monitoring committee

A management committee (MC) and a data safety monitoring committee (DSMC) have been established to ensure transparent and safe study practices.

The MC is responsible for developing the study protocol, training of all assessors and healthcare professionals involved in the intervention, and for the initiation of new study centers. Additionally, the MC will monitor the study procedures in all study centers and will ensure adherence to measurement and intervention protocols, as well as ethical guidelines. Deviations from any protocol will be documented and reported.

An independent data and safety monitoring committee (DSMC), consisting of experts in clinical studies, biostatistics, and perioperative and rehabilitation medicine, has been established to monitor recruitment, protocol adherence, and monitoring of follow-up and safety data. Virtual and face-to-face meetings will be regularly conducted, whereas both committees may independently request video conferences. The results of all meetings will be documented in protocols. The DSMC will assess the trial progress and safety, and accumulated trial data will be reported to the DSMC by the study statistician. As a primary responsibility, the DSMC will consider and assess treatment safety (e.g., serious adverse events (SAEs) or deaths). If necessary, recommendations will be made by the DSMC to the MC regarding stopping or continuing the trial. At their discretion, the DSMC may also formulate recommendations relating to the selection/recruitment of participants, their management, improving adherence to protocol-specified regimens and matter relating to patient retention, and procedures for data management and quality control.

The MC will be responsible for promptly assessing any DSMC correspondence or recommendations, to decide whether to continue or terminate the trial, suspend enrolment, or determine whether amendments to the protocol or changes in study conduct are required.

### Dissemination plans

The study report will be submitted for publication to a peer-reviewed medical journal and will be made available via the department’s website. Furthermore, a study report will be submitted to the Federal Joint Committee (G-BA).

A summary report of the final study results will be disseminated to all project partners and on the project homepage. Authorship in scientific publications will adhere to the recommendations of the International Committee of Medical Journal Editors [77].

## Discussion

PRAEP-GO is the first trial to investigate the effect of a shared decision-making conference combined with a 3-week prehabilitation program in a general surgical, (pre-)frail population. Until now, evidence is only available for a variety of specific surgical procedures [27]. Prehabilitation is, according to Wynter-Blyth and Moorthy, “a strategy to begin the rehabilitation process before surgery […]” [78]. Le Roy et al. emphasized the multimodal nature of prehabilitation and recommended the inclusion of (a) physical exercise training, (b) nutritional care, and (c) psychological support as part of the multimodal intervention during prehabilitation [79]. While these definitions offer a general idea of the concept and goals of prehabilitation, a broader and more specific framework on how to design such a program is mostly lacking. This is in part due to the fact that most prehabilitation trials focus on specific patient groups and/or surgical procedures.

Hughes et al. performed a systematic review and meta-analysis on prehabilitation programs before major abdominal surgery. They included 15 RCTs with 907 participants that reported on a variety of abdominal surgical procedures. In this review, prehabilitation leads to a significant reduction in morbidity, but not in LOS or functional recovery [80]. In contrast, Gillis et al. reported a significant reduction in length of hospital stay in a systematic review on prehabilitation, consisting of a nutritional intervention with and without additional exercises before colorectal resection surgery. Three out of nine RCTs that investigated functional outcomes reported a significant improvement [20]. In 2017, another systematic review on prehabilitation prior to abdominal cancer surgery included nine studies, and a total of 549 participants reported mixed results on functional walking capacity, cardiopulmonary fitness, anxiety, postoperative complications, and health-related quality of life. It is worthy to note that the prehabilitation programs varied considerably, with a program duration ranging between 2 and 8 weeks and a variety of therapeutic concepts that included one to three therapeutic modes (diet counseling, physical exercise, and psycho-social support) [81]. However, the physical exercise intervention consisted of walking and/or endurance exercises in all included studies. In another meta-analysis, nine studies with 435 participants receiving abdominal surgery were analyzed. The authors found a significant reduction in morbidity (OR 0.59 [0.38, 0.91] vs. control; OR 0.35 [0.17, 0.71] vs. usual care) and a significant reduction in postoperative pulmonary complications (OR 0.27 [0.13, 0.57] vs. control), but no significant reduction in LOS [82].

Regarding orthopedic surgical procedures, Gometz et al. performed a systematic review on prehabilitation before spinal surgery, including 5 RCTs with 217 participants. While none of the included RCTs reported any significant differences in pain or disability after surgery, 2 of these studies reported a significant reduction in total costs in the prehabilitation groups [83]. Wallis et al. reported on a systematic review and meta-analysis on preoperative intervention before knee or hip joint replacement surgery that included 23 RCTs with 1467 participants. The results of this review suggested that prehabilitation can significantly reduce preoperative pain and, when combined with educational intervention, is able to improve postoperative activity [84]. In another systematic review on prehabilitation before knee or hip arthroplasty surgery, Vasta et al. included 14 studies with 1175 participants. No robust conclusions could be drawn for hip patients; however, despite inconsistent evidence, most studies on knee patients reported postoperative improvements in pain, range of movement, quality of life, and functional scores [85].

For prehabilitation of older persons with frailty or pre-frailty, Milder et al. included 8 studies, with 2 of them ongoing. The six published studies included 168 participants and were highly heterogeneous, although five of the six could demonstrate positive effects, including improved function, reduced complication rates, and reduced mortality [86]. In another systematic review, Baimas-George et al. included 5 studies with 265 participants on prehabilitation in patients with frailty. Again, the included studies were heterogeneous but could demonstrate positive effects regarding LOS, mortality, and distance during 6-min Walk Test [87].

While several trials examined prehabilitation in specific settings, there is still a lack of robust evidence regarding its (cost-)effectiveness in a general surgical, (pre-)frail population.

A novel approach pursued in our trial is to include SDM into the concept of prehabilitation. As part of a European project aiming to identify factors for a successful implementation of integrated care, a mixed-methods study was conducted on the involvement preferences of geriatric patients [33]. While the results suggest that older people in acute need of care had a significantly lower inclination to be involved in a SDM process, qualitative interviews showed that the lack of a proper informational and educational process was at least in part responsible for their reluctance. The SDM process established in PRAEP-GO is based on specific recommendations for implementation of the process with frail older people [88]. To our knowledge, the inclusion of a SDM process into a concept of prehabilitation has not yet been investigated.

In contrast to most other studies in the field of prehabilitation, recruitment in PRAEP-GO is not limited to a single surgical intervention or indication, and the medical exclusion criteria preclude only urgent and intracranial procedures. The primary and many of our secondary endpoints reflect general factors contributing to health, QoL, and patient autonomy, factors that are critical in any evaluation of patient-centered interventions, regardless of the type of intervention.

This approach will result in a cohort that reflects the diversity of routine clinical practice. Being funded by the innovation fund of the Federal Joint Committee, the highest decision-making body of the joint self-government of physicians, dentists, hospitals, and health insurance funds in Germany, the intervention concept will be evaluated and considered for implementation in the routine care of the statutory health insurance funds in Germany.

### Choice of endpoints

Statutory health insurance in Germany generally covers all costs of medical treatments and nursing care assistance [89]. In the latter case, the need for care assistance must be evaluated with the NBA, by a specialized nurse or medical doctor, before care assistance payments can start [42]. In Germany, healthcare costs are based on the principle of solidarity, i.e., the payments of insured individuals are used to cover the costs of the care of those in need [89]. Therefore, statutory health insurance companies in Germany have a special interest, and even the obligation, to minimize costs by implementing preventive strategies [90]. Therefore, the primary endpoint is of particular interest for the German healthcare system, as the NBA was designed not only to evaluate whether a given person needs nursing care, but also if the costs of this care will be reimbursed by the insurance. The NBA assesses the level of care dependency based on reported difficulties in performing activities of daily living. While a validation study was conducted to evaluate the time and effort required for this care based on the different levels of care [91], there are no validation studies examining reliability or the existence of floor/ceiling effects. Nevertheless, the NBA has been selected as the primary endpoint as it enables an effective analysis from the patients’ perspective, with a clear indication of the impact the prehabilitation program can have from a health economic perspective. To compensate for the existing shortcomings of the NBA, several secondary outcomes will be investigated, including functional, cognitive, and psychosocial parameters, as well as outcomes related to medical care such as peri- and postoperative complications, LOS, and post-discharge utilization of the healthcare system.

